### Sample size and statistical analysis

Antibiotic duration is the main primary outcome of this on-going study. The expected standard deviation (SD) of antibiotic treatment, based on previous intervention trials [15-20] will be 6 days in both groups. Assuming a mean baseline antibiotic duration of 8 days, with a significance α-level of 5% and a power of 90%, 757 patients are needed in both groups. Patients that are discharged from the ICU before a stopping advice could have been issued and who are still being treated with antibiotics are considered “dropped out”. Assuming a drop-out rate of 20%, we need to include 908 patients in each group, so for the superiority margin in total 1816 patients will need to be included.

As the PCT intervention arm should be non-inferior, in terms of safety (mortality), in comparison to the standard treatment, the non-inferiority margin for PCT guided antibiotic management regarding 28-day-mortality is set on 8%. Based on previous trials, like the PRORATA-study [17], we assumed a 28% mortality rate in each group. With a one-sided significance α-level of 2.5% and a power of 90%, 714 patients are needed in both groups. Again with a drop-out of 20%, 1714 patients will need to be included. With such a sample size (and alpha 5% and beta of 20%) we would have been able to detect a 15% relative increase in mortality. Such conventional boundaries are very acceptable in most trials investigating the efficacy of new drugs. Here, we aim to do better, with an alpha of 2.5% and beta of 10%.

Losses to follow-up on both arms will be registered including the reason for loss to follow-up. Furthermore, the primary endpoint will be explored for association with potential prognostic factors in a survival analysis. The factors that will be considered are age, sex, APACHE IV-score, SOFA-score and usage of corticosteroids or dialysis.

The primary analysis population will consist of all randomized patients following the intention-to-treat principle. For the primary analysis, losses to follow-up (in both arms) will be included in the 28-day analysis of mortality and antibiotic consumption. The primary analysis will be repeated with the subset of patients who complied with the stopping threshold, as so-called “per protocol analysis” of mortality and antibiotic consumption on day 28.

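### The stated ability to detect a 15% relative increase in mortality does not follow from the protocol's own inputs, which give about 19–20% (one-sided) or 22% (two-sided)

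*Protocol article*

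**What the plan says.** All the relevant statements stand in one paragraph of the protocol article, section Sample size and statistical analysis.

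- Base rate: "we assumed a 28% mortality rate in each group".
- Margin: "the non-inferiority margin for PCT guided antibiotic management regarding 28-day-mortality is set on 8" percent. The Abstract and the Discussion give the same 8%.
- Size: "With a one-sided significance α-level of 2.5% and a power of 90%, 714 patients are needed in both groups".
- Inflation: "Again with a drop-out of 20%, 1714 patients will need to be included".
- Sensitivity: at alpha 5% and beta 20%, with that sample size, "we would have been able to detect a 15% relative increase in mortality".
- The paragraph calls such error rates conventional, and continues: "Here, we aim to do better, with an alpha of 2.5% and beta of 10" percent.

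For the sensitivity statement the article gives no formula, no sidedness and no base rate other than 28%.

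**The concern.** A 15% relative increase on 28% is 4.2 points. The formal design uses 714 per arm to exclude 8 points. Relaxing the error rates from 2.5% one-sided and 10% to 5% and 20% reduces the detectable difference, but it is not obvious that it could nearly halve it.

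The figure matters because the Background criticises the earlier French trial for using an absolute mortality margin where a relative one was called for, and the Discussion puts safety first. The 15% is the only relative mortality figure the article gives for its own design. If it is too small, a reader will credit the trial with more sensitivity to excess deaths than it has.

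**Working it through.** **Inputs** (all from Sample size and statistical analysis, except the last)

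- Mortality 28%. A 15% relative increase gives 0.28 × 1.15 = 32.2%, a difference of 0.042.
- Alpha 5%, sidedness not stated, so both are tried: z = 1.645 or 1.960.
- Power 80%: z = 0.842.
- Per-arm size: 714 before drop-out; 1714/2 = 857 after it; 908 as the final target (Abstract).

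**Step 1. The plan's own sample size reproduces.** A two-proportion comparison of 28% with 36%, two-sided 5%, power 90%, mean proportion 0.32:

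n = [1.960·√(2·0.32·0.68) + 1.282·√(0.28·0.72 + 0.36·0.64)]² / 0.08² ≈ 713 per arm.

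This agrees with 714 to within rounding. The usual non-inferiority formula with 28% in both arms, (1.960 + 1.282)²·2·0.28·0.72/0.08², gives 662, so 714 is adequate. Then 714 × 1.2 ≈ 857 per arm, or 1714 in total, as stated.

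**Step 2. Detectable increase at alpha 5%, power 80%.** Two forms were used:

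- Non-inferiority form: d = (z_alpha + 0.842)·√(2·0.28·0.72/n).
- Two-proportion test: the p2 at which 28% versus p2 has 80% power, with pooled variance under the null.

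For n = 857 the standard error is √(0.4032/857) = 0.02169. One-sided, d = 2.487 × 0.02169 = 0.0539, and 0.0539/0.28 = 19.3%. Two-sided, d = 2.802 × 0.02169 = 0.0608, or 21.7%. All results (non-inferiority form / two-proportion test):

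| Per arm | One-sided, points | One-sided, relative | Two-sided, points | Two-sided, relative |
|---|---|---|---|---|
| 714 | 5.9 / 6.1 | 21.1% / 21.7% | 6.7 / 6.9 | 23.8% / 24.6% |
| 857 | 5.4 / 5.5 | 19.3% / 19.8% | 6.1 / 6.3 | 21.7% / 22.4% |
| 908 | 5.2 / 5.4 | 18.7% / 19.2% | 5.9 / 6.1 | 21.1% / 21.7% |

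None of these reaches 15%.

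**Step 3. Power for 28% versus 32.2%.** In the non-inferiority form at 857 per arm, 0.042/0.02169 = 1.936. Power is Φ(1.936 − 1.645) = 0.615 one-sided and Φ(1.936 − 1.960) = 0.491 two-sided. The two-proportion test gives 0.599 and 0.474. At 908 per arm the two-proportion test gives 0.620 and 0.496; at 714 it gives 0.534 and 0.409. The stated power is 0.80.

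**Step 4. Size needed for the 15% claim.** 1414 to 1474 per arm one-sided, or 1795 to 1872 two-sided (non-inferiority form to two-proportion test). That is about 1.6 to 2.2 times 857.

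**Step 5. The stricter error rates.** At 857 per arm with 2.5% one-sided and 90% power, d = (1.960 + 1.282) × 0.02169 = 0.0703, or 25.1% relative. At a fixed size, stricter error rates make the detectable difference larger. The formal margin is 0.08/0.28 = 28.6% relative.

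**The case against.** The strongest reply is that the sentence is a counterfactual aside. The margin, the 714 per arm and the 1714 total stand without it, and the enrolment target of 1816 comes from antibiotic duration. That is correct, and it limits the weight of the point.

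A second reply is that the sentence says only mortality, and the safety endpoint also covers 1 year, when mortality would be higher. At 857 per arm a 15% relative increase would be detectable with 80% power if base mortality were about 40% (one-sided) or 45% (two-sided). But the document gives no 1-year rate, and the sentence follows directly on a 28-day calculation at 28%. The 28% reading is the natural one.

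Three stronger inferences are tempting and should not be drawn.

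- **That the cause is known.** Entering the total of 1714 as the size of each arm gives 15.3–15.7% two-sided. But 1428 per arm one-sided gives 14.9–15.2%, a one-sample variance gives 14.9% (714, one-sided) or 15.3% (857, two-sided), and the smallest observed difference reaching two-sided significance at 857 per arm is 15.2%. The document does not show which of these, if any, was used.
- **That the following sentence is false.** It names alpha 2.5% and beta 10%, which are stricter than 5% and 20%. Read as a statement about error rates it is fair. It is unclear only because it comes straight after a detectable difference.
- **That the ethics committee or the safety board was misled.** The Interim analysis section has the board working with the 8% margin and a p-value of 0.0294, not with 15%. Nothing shows that either body relied on this sentence.

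**Conclusion.** The point holds as an error in a stated sensitivity figure. At 28% mortality, alpha 5% and 80% power, 857 per arm can detect a relative increase of about 19–20% one-sided or 22% two-sided. Power for a 15% increase is about 60% or 48%. The 908 per arm finally planned does not rescue the figure, and if only 714 per arm are evaluable the gap widens.

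This rests on 1:1 allocation, the stated 28% base rate and standard normal-approximation formulas. Sidedness is left open because the document leaves it open; the conclusion is the same either way.

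A reader might infer that the safety design itself fails. It does not: the 8-point non-inferiority comparison is sized adequately on its stated assumptions. What the trial lacks is the finer sensitivity that this one sentence claims. The Discussion itself concedes that a smaller margin would need several thousand patients. The severity is moderate: a text correction, though of a figure that errs in the reassuring direction on safety.

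**What to change.** In Sample size and statistical analysis:

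1. Replace the 15% figure. For example: with 857 patients per arm, 28% mortality, alpha 5% and 80% power, the detectable increase is about 5.4–5.5 points (19–20% relative) if one-sided, or about 6.1–6.3 points (22% relative) if two-sided. Keep the version that applies and state its sidedness.
2. Preferably add that the formal 8-point margin equals a 28.6% relative increase at 28% mortality.
3. Keep the following sentence, but word it so that it plainly refers to stricter error rates and not to a smaller detectable difference.

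If the authors had another base rate or formula in mind, they should state it and show that it gives 15%.

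The cost is a few words. The margin, sample size, analysis and conduct do not change; the stated sensitivity becomes less favourable.

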### Treatment and intervention

The decision to start antibiotic treatment will in no way be affected by the trial. In all patients antibiotics will be started based on a clinical suspicion of infection or microbiological evidence of infection. This decision is fully at the discretion of the treating intensivist. Once antibiotics are administered for newly suspected or proven bacterial infection, patients or their legal representatives will be asked for informed consent. If informed consent is obtained, the patient will be randomised to either the standard therapy arm (control group) or the PCT arm (intervention group). Randomisation will be stratified for diagnostic group and study centre. When a patient is randomised for the control group, no PCT measurements will be performed. Other laboratory tests for infection such as CRP are allowed. When a patient is randomised for the PCT group, PCT will be measured at base-line called the T0-serum sample (T0: as close to initiation of antibiotics as possible, at least within 24 hrs). On the following days the ICU team will be provided with daily PCT values until ICU-discharge or until the third day after all systemic antibiotics have been discontinued. Along with daily PCT values a non-binding advice will be generated to consider stopping the prescribed antibiotics if PCT has decreased to <20% of its peak value (relative stopping threshold) or has reached a value of below 0.5 ng/ml (absolute stopping threshold). PCT levels will not be used to initiate antibiotic therapy. In case of two consecutive PCT levels below 0.5 ng/ml a stopping advice will be generated.

As for the control group, the physician will receive routine daily laboratory values as requested and no additional advice. Thus, treatment for both patient groups will be based on existing experience, expertise and local protocols, however, in the intervention group doctors are additionally provided with daily PCT levels, and a non-binding advice on continuation or discontinuation of antibiotic therapy by email, electronic patient data management system feedback, or research nurses. In both groups daily multidisciplinary reviewing will be performed on antibiotic therapy and duration, based on the clinical course, microbiological results and treatment guidelines. If doctors do not adhere to the stopping rules, reasons for non-adherence will be recorded.

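### The per-protocol set rests on a stopping threshold that only the PCT arm can meet; read literally it biases the supportive mortality and antibiotic comparisons, with mortality probably favouring PCT

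*Protocol article*

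**What the plan says.** All statements are in the Protocol article.

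- Sample size and statistical analysis sets the main population: "The primary analysis population will consist of all randomized patients following the intention-to-treat principle".
- The same section adds the per-protocol analysis: "The primary analysis will be repeated with the subset of patients who complied with the stopping threshold". Its endpoints are given as "of mortality and antibiotic consumption on day 28". It has no separate rule for controls, and does not say how to class a patient who dies or leaves the ICU before a threshold is met.
- Treatment and intervention says of controls: "When a patient is randomised for the control group, no PCT measurements will be performed". Their physicians get no additional advice.
- In the PCT arm, "a non-binding advice will be generated to consider stopping the prescribed antibiotics". The trigger is a fall to under one fifth of the patient's highest PCT, or a PCT under 0.5 ng/ml. On departures from it: "If doctors do not adhere to the stopping rules, reasons for non-adherence will be recorded".
- The sample-size text classes as drop-outs a further group, expected to be 20%: "Patients that are discharged from the ICU before a stopping advice could have been issued" and still on antibiotics.

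**The concern.** A control patient has no PCT value, so cannot comply or fail to comply with a PCT threshold. In the PCT arm, compliance needs a chain of events after randomisation: the patient survives, stays in the ICU, clears PCT far enough, and has a physician who accepts the advice. Patients who die before the threshold, or whose PCT never falls, were managed as the trial intended. The literal wording still drops them, with no counterpart dropped among controls. The comparison is no longer between randomised groups.

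This matters because the advice is non-binding. Overridden advice makes the two arms more alike, which pulls the intention-to-treat difference towards zero and helps a non-inferiority claim. A per-protocol analysis is the usual check on that, and it is the only one the article names. A check that conditions on surviving to the threshold could look reassuring when it should not.

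**Working it through.** **Inputs from the article:** 28-day mortality 28% per arm; margin 8%; one-sided alpha 2.5%; power 90%; 908 patients per arm; 20% discharged before advice.

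**Assumed, because the article gives no figure:** the share *f* of PCT-arm deaths that occur before a threshold is met (10-50%), and the 28-day mortality *m* of patients discharged early (5-15%).

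**1. The plan's own figure.** n per arm = [1.960·√(2·0.32·0.68) + 1.282·√(0.28·0.72 + 0.36·0.64)]² / 0.08² = 712.4, so 713 against the stated 714. This agrees with reading the margin as 8 percentage points absolute (28% against 36%).

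**2. Deaths before the threshold removed from the PCT arm, all controls kept.** With true PCT mortality *p* and x = f·p the share of the arm removed, per-protocol mortality is (p − x)/(1 − x). The chance of declaring non-inferiority is Φ[(0.08 − d)/SE − 1.96], where d = per-protocol mortality − 0.28, and SE is the unpooled standard error with 908 controls and 908·(1 − x) PCT patients.

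True PCT mortality 36%, exactly at the margin:

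| f | x | Per-protocol PCT mortality | d (points) | Chance of declaring non-inferiority |
|---|---|---|---|---|
| 0% | 0 | 36.0% | +8.0 | 2.5% |
| 10% | 0.036 | 0.324/0.964 = 33.6% | +5.6 | 19% |
| 20% | 0.072 | 0.288/0.928 = 31.0% | +3.0 | 62% |
| 30% | 0.108 | 0.252/0.892 = 28.3% | +0.3 | 95% |

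The whole excess disappears at x = 0.08/0.72 = 0.111, which is 0.111/0.36 = 31% of PCT deaths.

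With no true effect (p = 28%), f = 10% gives 0.252/0.972 = 25.9%, a false benefit of 2.1 points. f = 50% gives 0.14/0.86 = 16.3%, a false benefit of 11.7 points.

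**3. Early discharges removed as well, from the PCT arm only.** Per-protocol mortality becomes (p − x − 0.2m)/(0.8 − x).

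- With p = 28% and x = 0 it is (0.28 − 0.01)/0.8 = 33.8% for m = 5%, and (0.28 − 0.03)/0.8 = 31.3% for m = 15%. That is 5.8 to 3.3 points against PCT.
- The two biases cancel at x = 0.2(p − m)/(1 − p). For p = 28% this is 0.046/0.72 = 0.064 (m = 5%) or 0.026/0.72 = 0.036 (m = 15%), so 23% or 13% of PCT deaths. For p = 36% it is 0.062/0.64 = 0.097 or 0.042/0.64 = 0.066, so 27% or 18%.
- At the margin (p = 36%) the chance of declaring non-inferiority is then 0.2-4% for f = 20% and 6-38% for f = 30%, in place of 62% and 95%.

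**4. Where *f* might lie.** A simulation with no true effect used a lognormal time to threshold (sigma 0.6, median 4, 5 or 7 days). With deaths uniform over 28 days, 17-30% of deaths precede the threshold, and mortality among those who reach it alive is 24.4%, 23.4% and 21.5%. With early deaths (exponential, mean 8 days, capped at 28) the share is 42-59% and mortality is 18.5%, 16.7% and 13.9%. The false advantage is about 4 to 14 points. Putting the same shares into step 3 gives about −1.5 to +14.5 points. All timing inputs are assumptions.

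**5. Not quantified.** Overrides and patients whose PCT never falls are left out of the arithmetic. If these patients are sicker than average, removing them adds to the bias in favour of PCT.

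**The case against.** Four points on the other side carry weight.

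- **The wording has a second reading.** Complying could mean not overriding the rule. Treatment and intervention speaks of non-adherence as something the doctor does, and a patient who dies before any threshold has triggered no rule to break. On that reading early deaths stay in. This stands as a possible intent, but the per-protocol sentence does not say it. Nor is it only detail left to a fuller plan: the article states a rule, and the rule as written selects on one arm's data.
- **The direction is not fixed.** A reader might infer that the analysis must favour PCT. The article's own 20% early-discharge group also never reaches advice in the ICU and may well be low-risk. Removing it pushes the other way, as step 3 shows.
- **Intention-to-treat is primary.** A reader might infer that the trial's safety conclusion rests on the per-protocol result. Nothing in the article makes that result necessary or sufficient for non-inferiority, so the defect lies in a supportive analysis.
- **The antibiotic bias has no settled sign.** Compliers are selected for stopping when advised, which shortens courses. Early death also cuts antibiotic use short, so excluding early deaths raises the PCT-arm mean. No net figure can be derived from the article.

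**Conclusion.** The concern holds for the supportive analysis. Per-protocol membership is defined by a post-randomisation criterion that controls cannot meet, and taken literally it biases both the mortality and the antibiotic comparison.

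For mortality, bias in favour of PCT is probable but not certain. If only pre-threshold deaths are lost and all controls are kept, losing 10-30% of PCT deaths turns a 2.5% error rate at the margin into 19-95%. If early discharges are lost too, the net bias favours PCT only when more than about 13-23% of PCT deaths (true rate 28%) or 18-27% (true rate 36%) precede the threshold. These figures rest on assumed values of *f* and *m*. They show that the bias can be as large as the margin; they do not predict its size in this trial. The documents do not support saying that the analysis is certain to declare PCT safe, or that the primary conclusion is compromised.

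**What to change.** Reword the per-protocol definition before the final comparison by arm:

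1. Count a PCT-arm patient as non-adherent only when a stopping threshold was met and the advice was not followed.
2. Keep as adherent every PCT-arm patient who never met a threshold, including early deaths and early discharges.
3. Keep all controls. Apply any other exclusion, such as an eligibility violation, identically in both arms.
4. Report the remaining override-based comparison as supportive only, and base no safety claim on the threshold-complier subset.

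A complier-average or inverse-probability-weighted analysis may be added as a sensitivity analysis with its assumptions stated. The first needs randomisation to act only through following the advice, which is doubtful when clinicians see daily PCT values. The second needs daily severity data, and the article does not say that these are collected.

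The core change costs wording and a little more analysis; the reasons for non-adherence are already to be recorded. One limit remains: overrides are still a post-randomisation exclusion in one arm, so intention-to-treat must stay primary.

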### Interim analysis

The first interim analysis was performed after enrolment of 750 patients. Preceding this analysis the non-inferiority margin was set at 8% and a p-value of 0.0294 was used, corresponding with the performance of one interim-analysis in accordance with the Pocock method [21]. The DSMB examined the data and the trial would have been stopped immediately if the above predefined margins were reached. Furthermore, the DSMB reviewed the trial’s progress and adverse events according to treatment assignment.

### Duration

With the current inclusion rate of 50 patients per month, the total duration time is estimated at 36 months and the last patient is expected to be included around May 2013

## Discussion

### Published studies

The additional prognostic value of PCT in some critically ill patients has repeatedly been demonstrated. Until now six randomized controlled trials have been published that addressed the effectiveness and safety of PCT-guided strategy in antibiotic treatment of septic patients in adult intensive care units (ICU’s) [15-19,22], Several systemic reviews have been performed [23-28] and even an individual patient data meta-analysis in acute respiratory infections was published recently [14]. Thus, the question arises whether another study is warranted. The six trials were done with either small sample sizes or within highly selected populations [15-20]. Hochreiter [16] and Schroeder [8] both included patients after abdominal surgery. Svoboda et al. investigated 72 patients after abdominal surgery or surgery for major multiple trauma, using a semi-quantitative PCT assay [19]. Stolz et al. included 101 patients with only ventilator-associated-pneumonia [18]. Schuetz and colleagues have performed a individual patient data meta-analysis in patients with an acute respiratory infection [14]. This study combined 4550 patients with a suspicion of respiratory infection of which 598 patients were admitted to the ICU. Even in these severely ill patients the median duration of antibiotic treatment was reduced from 12 days to 8 days (P < 0.001). The two remaining studies have been published with a heterogeneous adult ICU population [15,17]. Remarkably, Nobre et al. excluded 203 out of 282 patients [15]. Due to strict exclusion criteria, this trial included only 79 patients.

Therefore, the PRORATA-study appears to be the only study with a larger number of adult patients in a heterogeneous critically ill population [17]. This study was designed as a both a start and stop study and comprised predominantly non-surgical patients (10% were surgical). Within the study a clear reduction of 2.7 days in antibiotic treatment duration was seen in the PCT arm. However, concerns exist about mortality statistics, the lack of power, and potential treatment bias. Furthermore, it is important to recognise that this study was performed in France, with one of the highest baseline antibiotic consumption rates in Europe. Therefore, it is important to investigate, in particular in a country with a relatively low antibiotic consumption, if PCT-guidance will lead to reduction of antibiotic use.

More recently, the PASS study was published [22]. This study was not intended to reduce antibiotic duration. The objective was to analyse whether PCT guidance was able to detect an infectious deterioration and could lead to improvement of the 28-day survival in 1200 ICU patients [22]. This trial did not show that a PCT-guided algorithm lead to improved outcome. In contrast, patients in the PCT arm had a longer LOS and used more antibiotics than the patients in the control arm.

